## Abstract

**Background:**

Optimal mental health is critical for a child’s learning and academic functioning. As a universal service, early education centres play an important role in promoting children’s mental health. Social-emotional learning programs are efficacious in reducing behavioural difficulties, enhancing competence, and improving learning abilities. Mindfulness practices, known to promote health and wellbeing in adults, have been adapted to education programs for younger populations, including pre-school children. Despite an increasing use of mindfulness-based programs in pre-school settings, there is a limited number of randomised trials and paucity of data on implementation fidelity of these programs. ‘Early Minds’ is a mindfulness-based program developed by Smiling Mind for 3–5-year-old children. This paper describes a protocol of a pilot randomised control trial, evaluating the implementation of the program in early learning centres (ELCs, i.e. pre-schools) in Melbourne, Australia. The primary aim of this pilot study is to examine the feasibility, acceptability, and fidelity of the program. The secondary aims are to assess the acceptability of the design and measures and to investigate preliminary impacts of the program on child social-emotional outcomes.

**Methods:**

A convenience sample of six ELCs are recruited. Participants include educators, children, and their parents from 3- and/or 4-year-old ELC rooms. Upon completion of baseline surveys, rooms are randomly allocated to intervention and control arms by an independent statistician. ‘Early Minds’ is designed in a flexible delivery manner; meditations and activities are completed at least three times a week. Educators are trained in the program and have access to the activities and meditations on an app. Parents are encouraged to practice with their children at least three times a week. Educators document implementation fidelity throughout the 8 weeks of the program. Parents and educators complete follow-up surveys at 3 and 12 months post-randomisation, capturing feasibility and acceptability, child social-emotional behaviour and sleep, and educator, parent, and family wellbeing outcomes.

**Discussion:**

This pilot study is the first to assess a mindfulness-based program in ELCs in Australia. Data on feasibility and acceptability, implementation fidelity, and potential impact on children’s behaviour will inform the design of adequately powered evaluation trials.

**Trial registration number:**

Australian New Zealand Clinical Trials Registry, ACTRN12618000435280. Date registered 26 March 2018.

## Background

Young children’s mental health has an important role in shaping their learning skills and future outcomes [1–3]. Optimal mental health is achieved not only by eliminating difficulties or symptoms, but also by promoting competence, with optimal mental health being a combination of low difficulties and high competence. Mentally healthy young children are free of not only externalising and internalising symptoms but also succeeding in the cognitive and emotional developmental tasks of their age, gaining skills that lay the foundations for the successful adaptation to future challenges [4, 5]. These include emotion regulation skills—understanding and managing emotions, social skills—getting along with others and empathising, and executive functioning skills—planning, making decisions, and regulating attention [6]. When young children have mental health difficulties and/or low competence to deal with their emotions, behaviours, and relationships, this impairs their ability to learn and function in school. Evidence shows that anything less than the optimal combination of low difficulties and high competence is associated with poorer learning skills and achievements [7, 8]. As a universal service, early learning centres (ELCs) and schools play a key role in developing mentally healthy children, and there is increasing recognition of the importance of acquisition of social-emotional skills in early education contexts [9, 10]. Social-emotional learning (SEL) programs in schools have been shown to improve not only children’s wellbeing but also their academic achievements and learning skills [10–12]. Although all children may benefit from interventions that build their social-emotional skills and executive functioning, evidence suggests that those with higher difficulties at baseline benefit the most [10].

Mindfulness refers to a Buddhist meditation practice that cultivates present moment awareness by paying attention to present experience in the present moment, with openness and without judgement [13]. The ability to direct attention and focus on one thing, and an open, non-judgmental attitude, is developed through the practice of meditation. Mindfulness training has become a common practice in various health settings over the last decades, with robust evidence in clinical adult populations of efficacy in reducing mental health symptoms and improving socio-emotional functioning [14–16] also shown in neural changes in the brain and immune function [17, 18].

More recently, there has been increasing use of mindfulness practices with younger populations. The vast majority of interventions have been conducted with middle and high school students, with some evidence of efficacy for neurocognitive, psychosocial, and psychobiological outcomes [10, 19–21]. Mindfulness programs have recently been extended and adapted to the pre-school age, implemented mostly in early education settings. Results from controlled and non-controlled studies with pre-schoolers show initial promise in reducing externalising symptoms and behavioural problems and hyperactivity [22–25] and in promoting self-regulation skills and executive functions [25–32], prosocial behaviour [22, 28], and language and reading skills [26]. Notably, most studies involving mindfulness practice with children are not randomised control trials and have substantial methodologic limitations, with small sample sizes and potentially biased reported outcomes [19, 21]. Thus, despite some evidence of efficacy, with increasing delivery of programs, there is still a practice-research gap, calling for a stronger evidence base for these programs. Additionally, the literature on programs to improve developmental outcomes and mental health shows that there is considerable variability in the actual delivery of programs in real-life conditions [11, 33]. Implementation fidelity, i.e. the extent to which the program is delivered in the way it was designed, is critical for its efficacy and can also help to understand which elements of the program work for whom and in which contexts. There is a paucity of data on implementation fidelity for mindfulness programs in educational settings [34].

### The Early Minds program

The Smiling Mind Education Program (SMEP) is described by the Smiling Mind organisation as a pre-emptive mental health and wellbeing curriculum, designed to provide accessible and flexible mindfulness educational resources for primary and secondary school teachers, students, and parents. The program includes training modules and a manual for educators, access to the activities and meditations via the Smiling Mind website and app, and a resource guide for parents. The topics covered in the program include awareness, attention, the senses, savouring, movement, recognising emotions, managing emotions, self-compassion, optimism, strengths, gratitude, making decisions, setting goals, empathy, acts of kindness, positive relationships, positive communication, a curious mind, growth mindset, and resilience [35].

An evaluation of an 8-week implementation of the SMEP [36], involving 12 Victorian primary and secondary schools, 1853 students, and 104 teachers, yielded promising results for both teacher and student outcomes. In this controlled trial, at 8 weeks post-intervention, students in SMEP reported a significant increase in their wellbeing and sleep quality, improved sense of safety at school, and reduced classroom disruptions, compared to control group peers. Students reporting greater distress at baseline tended to report greater benefits of the program. Teachers in the SMEP reported improved concentration, sleep, and wellbeing and reduced stress and tension [36].

Based on the success and uptake of the program in primary and secondary schools, Smiling Mind, together with Early Childhood Australia, psychologists and learning experts developed the Early Minds program—a version of the SMEP adapted for pre-schoolers. The adaptation to the pre-school years included simplifying the topics, aligning them with the Australian Early Years Framework [37], and developing short meditations and additional activities that are more suitable and engaging for young children. Two versions of the program exist—one for 3–4-year-old children and one for the 5–6-year-old children. The simplified topics in the Early Minds program include the following: Who am I, Me and My World, At My Best, I love to Learn, and Finding My Voice. Each topic includes one meditation, one mindfulness activity, and two mindful movement activities. Mediation is a formal mindfulness practice, bringing the attention to a point of focus—e.g. focusing on breathing; mindfulness activity is considered an informal practice, through which mindful awareness is brought into daily activities and tasks by engaging all senses and focusing all the attention on the task—e.g. drawing your family while paying attention to the feeling in the hand and the sounds created by using pencil and paper, the colours on the page, and the feeling and thoughts occurring while drawing; mindful movement activities are ‘movement meditations’, which combine elements of formal and informal mindfulness practice—e.g. imitating and learning each other’s or animal movements while becoming aware to the sensations and feelings of the different movements. Smiling Mind and Early Childhood Australia have enlisted the Murdoch Children’s Research Institute (MCRI) to conduct an independent evaluation of the Early Minds program pilot in early learning centres (ELCs) in Melbourne, Victoria.

### Aims and objectives

The primary objective is to evaluate the feasibility, acceptability, and implementation fidelity of the Early Minds program in six Melbourne ELCs. The secondary objectives are to pilot measures of educator and parent-reported child outcomes and investigate preliminary impacts of the program on child, parent, and educator wellbeing and family functioning compared to children and families who do not receive the program. Results of the study may be used to inform the design of a large-scale trial.

### Overall study design and setting

This is a pilot cluster randomised controlled trial, evaluating the implementation of the 8-week Early Minds program by Smiling Mind within ELC rooms compared to standard ELC curriculum. The study involves three points of data collection: baseline and 3- and 12-month post-randomisation follow-up. Parents and educators complete study surveys at baseline, 3 months, and 12 months. Recruitment and training are conducted by Smiling Minds, and the data collection and evaluation are conducted by MCRI. Educator mindfulness-based knowledge, user experience, competence, and actual use of the program inform feasibility, acceptability, and implementation fidelity. Acceptability of the design and measures is assessed by the response rates of educators and parents and completion of the surveys and inform larger trials. Children’s socio-emotional functioning, sleep, and behaviour, reported by parents and educators, and educator and parent wellbeing will indicate potential outcomes of the program.

## Methods and analyses

### Setting

This is a community-based study, set in six ELCs, representing a sample of convenience in the Melbourne metropolitan area. Within each ELC, children are divided into rooms, based largely on their age at the start of the calendar year, i.e. 3-year-old or 4-year-old rooms.

### Participants

Participants are educators within the 3- or 4-year-old rooms at ELCs recruited by Smiling Mind, children who attend the rooms, and their parents. Centres where the majority of families are non-English speaking or with fewer than 15 children per room are not eligible to participate. Children are excluded if their parent’s English language skills preclude their ability to provide informed consent and complete the study surveys, written at a grade 6 reading level.

### Timeline (see Fig. 1).

This study involves three points of data collection: baseline and 3- and 12-month post-randomisation follow-up. Randomisation takes place after baseline data collection.

**Fig. 1 Fig1:**
[figure not shown]
Consort flow diagram

#### ELC recruitment

Recruitment of the ELCs is conducted by Smiling Mind. Following discussions by Smiling Mind with potential ELC Directors regarding the requirements and time commitments involved and assessing eligibility, an agreement is signed with interested centres. Following the ELC recruitment, the research team visits the centre and describes the study procedures to the educators who then sign a Memorandum of Understanding, agreeing to participate in the study. Educators then complete the baseline survey, reporting demographic information and their current experience and knowledge of mindfulness.

#### Child and parent recruitment

All families of children in participating rooms receive information letters, advising that their ELC is participating in the mindfulness evaluation study, that some educators will be trained in the program and others will not, that the trial intervention will go ahead regardless of child/parent participation in the evaluation study, and that the research team will contact the parents to explain more. An ‘opt-out’ approach is used, and parents are asked to return their ‘opt-out’ slip to their ELC if they do not want to be contacted by the study team. If parents do not opt-out within 2 weeks, the centre provides the research team with the family’s contact details and the research team telephone the family to provide further details and assess eligibility. Following this telephone call, interested and eligible parents are sent the study information statement, consent form, and baseline survey via post or email. Upon receipt of the parent survey and consent, the child’s educator is emailed a link to a baseline survey to complete for this child.

#### Randomisation of classes

Upon receiving the completed baseline parent and educator evaluation and child surveys, an independent research assistant randomises ELC rooms to either the program/intervention group or the usual care/control group, stratified by ELC room age (i.e. 3- or 4-year-old room) to ensure younger age rooms are represented in both the program and usual care groups. Children and educators are randomised to the same arm as their room. The independent research assistant conducts the randomisation by selecting a random seed and running a random number sequence using syntax written by an independent statistician. Only educators within the intervention arm are trained in the intervention to reduce contamination in control rooms, particularly if one ELC has an intervention and a control group. Educators and families receive letters to inform them of their group allocation; thus, participants are not blind to allocation. Study staff who are responsible for communication with ELCs and parents are not blind either. However, quantitative analyses will be conducted by research team members who have access only to de-identified data and thus will remain blind to group allocation throughout the analyses.

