### Outcomes

Primary outcomes are program feasibility, acceptability as reported by educators and parents, and implementation fidelity as reported by educators. Secondary outcomes are acceptability of the study design and measures by educators and parents, child social-emotional behaviour and sleep as reported by educators and parents, and educator and parent wellbeing.

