#### Implementation fidelity

During the 8 weeks of the program, participating educators in the intervention group are asked to complete a daily fidelity checklist. This checklist documents for each activity/meditation the group size (whole group or small group), to what extent it was completed (all, partial), whether children were distressed by the activities (yes/no), and number of times the activity was done that day.

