#### Educator program evaluation surveys

At 3- and 12-month post-randomisation, all educators complete an evaluation survey, repeating the baseline assessment of their knowledge and practice of mindfulness, wellbeing, and class climate. Educators in the intervention group are asked about their use and experience of delivering the program.

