#### Parent surveys

At 3- and 12-month post-randomisation, all parents complete a survey, repeating the baseline measures of their child’s social-emotional behaviour and sleep, their own mindfulness and wellbeing, and their parent-child relationships. Parents in the intervention group are asked about their use of the program meditations and activities via the Smiling Mind app and their experience of using them.

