#### Missing data

Where available, we will follow the instructions for each specific outcome measure regarding how to deal with missing data. We will then describe the extent of missing data for the variables in our measures and seek to determine identifiable factors associated with missing data—i.e. was missingness at random or associated with certain characteristics such as family socio-economic status. We are planning to conduct an intention-to-treat analysis as we aim to describe the possible impacts of the program as it would be delivered in ‘real life’ in an early childhood setting and collect data from educators on the types and frequencies of activities. In (hypothetical) cases that an educator was allocated to intervention arm but has not done any activity during the intervention period, we will conduct a complementary per protocol analysis.

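### De-identification does not mask the arm, so it cannot keep the analysts blind throughout the analyses as the protocol states

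*Protocol article*

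**What the plan says.** Under Randomisation of classes, the protocol article explains that participants are told their allocation, and adds: "Study staff who are responsible for communication with ELCs and parents are not blind either". It then says the quantitative analyses fall to research team members "who have access only to de-identified data and thus will remain blind to group allocation throughout the analyses". De-identification is the only mechanism named, and blinding is presented as its consequence.

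Other sections define data that only one arm supplies:

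- Implementation fidelity: "participating educators in the intervention group are asked to complete a daily fidelity checklist", over the 8 weeks of the program.
- Educator program evaluation surveys, at 3 and 12 months: "Educators in the intervention group are asked about their use and experience of delivering the program".
- Parent surveys, at 3 and 12 months: "Parents in the intervention group are asked about their use of the program meditations and activities via the Smiling Mind app", and about their experience of using them.

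The Outcomes section puts this material at the centre of the study: "Primary outcomes are program feasibility, acceptability as reported by educators and parents, and implementation fidelity as reported by educators". The Missing data section adds that, if an educator allocated to the program carried out none of it, "we will conduct a complementary per protocol analysis".

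**The concern.** The blinding sentence makes two assertions: that stripping identifiers leads to blindness, and that the blindness lasts through all the analyses. The first confuses confidentiality with masking. A record can be anonymous and still show which arm it belongs to. The second sits badly with a study whose primary outcomes come largely from fields that exist in one arm only.

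The point matters because this is the only blinding the trial claims. Parents and educators know their allocation and also report the child outcomes, and the Discussion accepts that blinded external assessment was not feasible. There are many child, parent and educator scales, two informants for the child outcomes, and planned exploration of factors associated with missing data. Analysts who know the arm could let that knowledge influence their choices, while readers would believe they were protected against it. The mean differences between arms are intended to inform the sample size of a later trial.

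**Working it through.** No figure is stated on this point and no arithmetic applies. The check sets the blinding claim beside the data each arm supplies and the analyses planned.

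1. **Does de-identification imply blindness?** De-identification removes what links a record to a person. Allocation is a property of the room and is not an identifier of that kind. It stays visible unless it is separately coded or withheld, and the article states no such step. The inference fails whatever the analysts' file contains.

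2. **Which data differ by arm?**
   - Both arms: the parent survey scales, the educators' own measures, and the educators' 3-month ratings of each child.
   - Intervention arm only, as stated in the text: (a) the daily fidelity checklist; (b) educator use and experience; (c) parent app use and experience.
   - Count: three blocks. Table 1 also lists rows for user experience and evaluation of implementation, but as reproduced it does not mark them as confined to one arm, so they are not counted separately.

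3. **What would one such entry reveal?** Rooms are the unit of randomisation, and children and educators take the arm of their room. The Analysis plan models clustering by classroom, so a room identifier must be in the comparison file. A single completed entry from (a), (b) or (c), linked to a room, shows that room to be an intervention room. If arms were coded A and B, the same entry would decode the label for every room.

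4. **Can the planned analyses all be done blind?**
   - Between-arm comparison of outcome scales: yes. It needs outcomes, a room code and a coded arm, and nothing from (a) to (c).
   - Fidelity and program-use summaries: no. The data come only from the intervention arm.
   - Per-protocol analysis: no. Its trigger combines true allocation with the record of activities done.

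Blindness is therefore feasible for the first kind of analysis and not for the other two. Even for the first, it depends on coding and separating the data, which is not the mechanism stated.

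**The case against.** The strongest reply is that the article does not describe the contents of the analysts' file. It does not say that the file carries an arm variable, or that these analysts receive the checklist or program-use items. Coded labels and split exports are data-handling details that a condensed article may leave to a fuller protocol or analysis plan. The blinding sentence is also restricted to quantitative analyses. The Analysis plan first describes descriptive reporting, including frequency of program use and barriers, and then turns to quantitative data, with intention-to-treat and multilevel comparison. On that reading most intervention-only material lies outside the claim. The per-protocol analysis is complementary, and the authors call its trigger hypothetical. Finally, the study is a pilot not designed to determine efficacy, and it discloses its unblinded participants, staff and reporters.

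Much of this stands. A reader might infer that the analysts will in fact be unblinded, or that the arm comparison is biased. The documents support neither inference, because they do not show what the analysts hold and masking of that comparison is feasible. The consequence is also modest.

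Two things are not answered. The stated reason for blindness is wrong, and further detail elsewhere would replace it without making it valid. The scope is also too wide: checklist counts and frequency of use are numerical data, so the boundary of the quantitative analyses is unclear, and the per-protocol analysis, if triggered, requires true allocation.

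**Conclusion.** The point holds as a wrong stated mechanism and an overstated scope for the only blinding the trial claims. De-identification does not mask the arm. Three intervention-only data blocks would reveal it to any analyst who sees one of them linked to a room, and blindness cannot last through all analyses if the per-protocol analysis is run. It can be achieved for the between-arm outcome comparison.

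The conclusion rests on the article's wording and its data structure. It does not assume that analysts will receive the intervention-only fields. The size of any bias cannot be derived from the document. It is likely smaller than the bias from outcome reports by parents and educators who know their allocation. The correction is worth making because it is cheap and the present wording gives readers an assurance that the stated mechanism does not support.

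**What to change.** Have someone outside the analysis team prepare a comparative file with the arm coded A/B, rooms under neutral codes, and all fidelity and program-use fields removed. Complete the intention-to-treat comparison on that file. Only then release the program-use and fidelity data and, if it is triggered, the material for the per-protocol analysis. If feasibility results are wanted sooner, a different team member can analyse them separately.

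Reword the sentence under Randomisation of classes to name this mechanism and to say that analysts are blind until the between-arm comparison is complete. If the split is not carried out, remove the claim.

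The cost is a small data-preparation task and one revised sentence. The independent research assistant could do the preparation, but the article gives that person only the randomisation, so it would be a new duty. No additional data collection is needed.
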